## Methods/Design

Study of predictive evaluation of a tool to assess the risk of osteoporotic fracture through the follow up of a cohort initiated in 1999.

## Study population and enrolment procedures

This multicentre study is carried out by family practitioners and other specialists who refer patients to the same reference centre for undertaking BMD. The criteria for referral follow the recommendations of the WHO of not performing a population screening but to select cases among those of greatest risk of having osteoporosis and subsequent osteoporotic fractures or the follow up and control of patients already receiving treatment.

*The FRIDEX cohort (Factors of fracture risk and central bone densitometry)*. This cohort is constituted of men and women referred by general practitioners and specialists for undergoing central bone densitometry by *Dual-energy X-ray absorptiometry *(DXA) for the initial study of osteoporosis or treatment follow up, who accept to answer an extensive questionnaire on risk factors (RF) for osteoporotic fracture (family history of osteoporosis and hip fracture, clinical risk factors and lifestyle habits related to diet and toxic substances) [see Table 1]. This cohort was initiated in 1999 at the Bone Densitometry Unit of the Department of Nuclear Medicine of the University Hospital Vall d'Hebrón in Barcelona and at the end of 2009 had included 25,783 persons of both genders who had undergone a total of 41,849 DXA and questionnaires on RFs.

**Table 1 T1:** Total FRIDEX (2000-2010 years) cohort description

		Total	Men	Women
Cases		25,783	2,349	23,434

		N (SD)	N (SD)	N (SD)

Age		61.2 (10.2)	65.0 (10.8)	60.8 (10.1)

Weight		68.1 (12.2)	75.3 (13.3)	67.4 (11.9)

Height		155.6 (7.4)	165.7 (7.2)	154.6 (7.4)

		N (%)	N (%)	N (%)

Parental Osteoporosis or Fracture	Yes	4,220 (16.4%)	153 (6.5%)	4,067 (17.4%)
	No	21,524 (83.6%)	2,192 (93.5%)	19,332 (82.6%)

Parental Hip Fracture	Yes	166 (6.3%)	10 (2.6%)	156 (6.9%)
	No	2,462 (93.7%)	372 (97.4%)	2,090 (93.1%)

Previous Fractures	Yes	6,865 (26.6%)	837 (35.6%)	6,028 (25.7%)
	No	18,918 (73.4%)	1,512 (64.4%)	17,406 (74.3%)

Current Prescriptions	Yes	13,928 (54.0%)	1,048 (44.6%)	12,880 (55.0%)
	No	11,855 (46.0%)	1,301 (55.4%)	10,554 (45.0%)

Since the beginning of the study verbal informed consent to participate in the cohort was obtained from all the patients and an extensive questionnaire on clinical risk factors was carried out. The data collected is stored in a specific database (DB) for this cohort.

Informed consent to participate is requested in the reference centre and a questionnaire on risk factors (QRF) for osteoporotic fractures is given during the visit and anthropometric parameters are determined. Ten years after the first QRF and DXA the patients are asked to answer a phone survey (See additional file 1) to know the evolution of the study variables and outcomes (fragility fractures).

## Study population

Urban setting. Primary care (PC), extrahospitalary (E) and hospital specialties (H).

Integrants of the FRIDEX cohort. Randomised sample (simple computerised randomisation stratified by sex) of men and women from 40 to 90 years of age in the FRIDEX cohort for 10 years since the baseline DXA and QRF. At the end of 2009 this sub-cohort included 5,813 persons recruited from January 1 to December 31, 2000.

## Eligibility Criteria

A total of 3,684 subjects were randomised, 9.3% being males to maintain the original proportion of the global study cohort.

## Inclusion criteria

The study subjects were Caucasians, ≥ 40 and ≤ 90 years of age at the time of inclusion in the FRIDEX cohort, understood and spoke the Spanish language, were able to respond to the initial and/or follow up telephone questionnaire (TQ) and accepted to participate in the study providing the corresponding informed consent. Physically or psychically handicapped patients were included if the relatives or care providers accepted to answer the TQ.

## Exclusion criteria

Subjects < 40 or > 90 years of age at the time of the first DXA and QRF were excluded since FRAX™ does not allow the calculation of the adjusted risk outside this age range. Patients with physical or psychic limitations impeding their participation and whose relatives did not accept to respond to the TQ were excluded as were those with Paget's disease, cancer with bone involvement or disease which may simulate osteoporosis (i.e. myeloma). Patients of ethnic groups other than Caucasian were not included since other studies have demonstrated different risk characteristics. Patients not providing consent to respond to the TQ and those without a telephone to contact or did not respond after 3 calls made at different times according to the procedure manual were also excluded from the study.

Sample Size (figure 1):

For the main objective (predictive validation of FRAX™ it has been calculated that a sample of 1,070 individuals are needed in a bilateral contrast to guarantee that the sample estimates the percentage of incidence of new fractures with a precision of 3%. If an annual loss rate of 1% during the 10 years of follow up of the study is considered, a sample of 1,177 subjects is required. In the pilot study carried out in April 2009 in a randomised sample of 149 cases with three telephone calls / person, 47 persons could not be contacted (31.5%). One hundred two (68.5%) were contacted, of which 3 (4.9%) living patients and the relatives of 2 dead patients refused to participate. Cases receiving anti-osteoporotic drugs and/or those with cancer (35 people) and 6 males were excluded. Information was obtained on data at 10 years in 97 of the 149 cases. A total of 3,664 individuals should therefore be contacted, thus our population of 5,813 subjects potentially eligible guarantees the necessary sample size.

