**Figure 1 F1:**
[figure not shown]
**FLOW CHART study**. Participant's selection.

Finally, in the pilot study of 149 patients and after fulfilling the exclusion criteria we obtained a sample of 56 (37.6%) of the 149 cases. With more conservative calculations, a maximum of 3,056 subjects should be contacted plus 20% for safety. Thus 3,664 persons should be contacted, therefore our originally recruited population of 5,813 subjects greater than 40 years of age included in the cohort until the end of 2000 sufficiently guarantees the necessary sample size. Consequently, 3,664 subjects were randomly selected from the 5,813 patients included in the cohort during the year 2000.

A sample will be obtained by months in the year 2000. Ordering will be performed using randomised numbers for each month and the calls will be made in this order until the required number is achieved. The approximate calculation is of 317 cases / month with a range from 190 to 395 cases in the different months of 2000, and the calls will be made until the figure calculated per month is met.

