### Analysis plan

The characteristics of the population will be described according to univariate descriptive analysis. Simple comparisons of the baseline characteristics will be made among the participants and non participants of the cohort. The Chi-square test will be used to evaluate the association between qualitative variables. The Student's t-test or, if necessary, its non parametric equivalent, the Mann-Whitney U test, will be implemented to evaluate the differences in the distribution of a quantitative variable according to the categories defined by a binary exposure. To assess the differences in the distribution of a quantitative variable according to the categories defined by a categorical variable with more than 2 categories, ANOVA analysis of variance or its corresponding non parametric test (Kruskal-Wallis) will be used.

For the predictive validation of the FRAX™ tool, the appearance of the first fracture occurring during the follow up period will be taken into account. The validation of the results obtained with the FRAX™ will be performed with the Hosmer-Lemeshow test and the calculation of the ROC curve. This test divides the participants into groups (normally 10) based on their estimated risk of fracture (FRAX™) and confirms that each group presents a number of cases of incidental fractures adjusted to the predicted number. On the other hand, the ROC curve considers the scale of FRAX™ risk as a diagnostic test of the presence of future fractures and as such leads to different calculations of sensitivity and specificity changing the cut off point selected. Finally, both probabilities (sensitivity and the complementary of specificity, or 1- specificity) will be graphically represented the curve. The shape of the curve is a visual indicator of the quality of the diagnostic test.

To know the distribution of the factors associated with fracture according to age and sex, bivariate combinations will be used with the Chi-square test among categorical variables and the Student's test among quantitative and categorical variables. To model the number of fractures occurring in our dataset which is, in fact, a count over time, Poisson regression will be used, which is what is precisely required for this type of variables and was used for the creation of the FRAX™ scale. All the statistical tests will be undertaken with a confidence interval of 95% and with the use of the 17th or latest version available of the SPSS statistical package.

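### The pilot yield that sizes the study drops treated patients, cancer cases and men, but the written eligibility criteria do not, so the population for the FRAX validation is contradictory

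*Protocol article*

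**What the plan says.** Four parts of the protocol article bear on who is validated.

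- **Pilot and sizing (sample-size text under Exclusion criteria, continued after Figure 1).** Of 149 sampled, 47 could not be contacted and 5 refused (3 living patients, relatives of 2 deceased), leaving 97 with ten-year data. Then: "Cases receiving anti-osteoporotic drugs and/or those with cancer (35 people) and 6 males were excluded". The text after Figure 1 says that "after fulfilling the exclusion criteria we obtained a sample of 56 (37.6%) of the 149 cases", and goes on to 3,056 to contact, plus 20%, giving 3,664.
- **Exclusion criteria.** The list covers age outside 40 to 90, limitations preventing participation without a relative's help, Paget's disease, "cancer with bone involvement or disease which may simulate osteoporosis (i.e. myeloma"), non-Caucasian ethnicity, lack of consent, and failure to make telephone contact. It contains no treatment criterion and no sex criterion. The inclusion criteria add neither.
- **Study population and Eligibility Criteria.** The sample is of men and women, stratified by sex, with "9.3% being males to maintain the original proportion of the global study cohort".
- **Study population and enrolment procedures.** The reasons for referral include "the follow up and control of patients already receiving treatment".

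The Analysis plan compares observed fractures with FRAX predictions by the Hosmer-Lemeshow test and a ROC curve. It states no restriction, stratification or adjustment for anti-osteoporotic treatment.

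**The concern.** The pilot figure is described as the result of applying the exclusion criteria, yet it can be reached only with three exclusions that the list does not contain: anti-osteoporotic drugs, cancer in general, and male sex. On men the conflict is direct, since other sections keep them on purpose.

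This matters because the main objective is a comparison of observed with predicted fractures. The article's description of FRAX does not mention treatment as an input, although it does not list every input. If treated patients are included and treatment works, observed fractures fall while the prediction does not. A calibration gap could then be read as a fault in FRAX, and the Discussion intends to use the results to recalibrate its parameters. Whether treated patients are in or out therefore changes what the main result means.

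The pilot rule also does not say whether drug use was judged at the baseline DXA or at any time up to the 2009 call. Removing people who started treatment during follow-up would select on information that arose after the prediction was made.

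**Working it through.** **1. Reproduce the plan's base number.** The stated requirement is "a sample of 1,070 individuals are needed in a bilateral contrast to guarantee that the sample estimates the percentage of incidence of new fractures" with 3% precision. With p = 0.5 (the conservative choice, not stated) and two-sided 95% confidence: n = 1.96² × 0.25 / 0.03² = 1,068 after rounding up, against 1,070 stated. Allowing 1% loss a year for ten years as a simple 10% addition: 1,070 × 1.10 = 1,177, as stated.

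**2. Reproduce the pilot yield.** 149 − 47 = 102; 102 − 5 = 97; 97 − 35 − 6 = 56; 56/149 = 37.6%. This matches exactly, and only if all 41 removals are applied.

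**3. Find which yield drives the contact number.** Number to contact = 1,177 / yield, then × 1.20. Participants = 3,664 × yield.

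| Rule | Yield | To contact | Plus 20% | Participants from 3,664 |
|---|---|---|---|---|
| Pilot rules (drugs, cancer and men out) | 56/149 = 37.6% | 3,132 | 3,758 | 1,377 |
| Men kept, drug/cancer cases out | 62/149 = 41.6% | 2,829 | 3,395 | 1,525 |
| Written criteria (none of the 41 removed) | 97/149 = 65.1% | 1,808 | 2,170 | 2,385 |

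The plan states 3,056 and 3,664. The first row is within 2.5% of both, and 3,056 × 1.2 = 3,667. The other rows do not fit. The sample-size paragraph also gives 3,664 directly after the figure of 97 in 149, but that yield leads to 2,170. So the sizing rests on the pilot rules.

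The last row is approximate: a few of the 35 may have had bone-involving cancer or myeloma, which the written list does remove.

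**4. How much of the pilot is in dispute.** Drug and/or cancer cases: 35/97 = 36.1%. All disputed removals: 41/97 = 42.3%.

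**5. What treatment could do to calibration if the written list governs.** For a perfectly calibrated FRAX, with treated patients at average risk and a constant effect, observed/expected = 1 − (share treated) × (risk reduction). The documents give neither a treated share separate from cancer nor a treatment effect, so this is illustration only.

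- Share 36.1% (upper bound from the pilot): 1 − 0.361 × 0.20 = 0.93; 1 − 0.361 × 0.50 = 0.82.
- Share 10% (assumed lower value): 1 − 0.10 × 0.20 = 0.98; 1 − 0.10 × 0.50 = 0.95.

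**The case against.** The strongest reply is that the arithmetic itself shows the intention. Only the 56/149 yield comes close to 3,056 and 3,664, so the authors evidently expected to remove treated patients. The printed list may simply be an incomplete condensation, and the participant flow chart that might settle it is not available. Read that way, most of the treatment problem disappears. This stands as far as it goes: a reader might infer that the validation is biased toward FRAX over-predicting, and the documents do not support that as an unconditional claim. It does not remove the contradiction. If the pilot rules govern, the list is wrong on treatment and cancer, and the sections that keep men conflict with the sizing.

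Other limits also stand.

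- The written criteria do not keep every cancer patient. Bone-involving cancer and myeloma are already out, so only other cancers are in conflict.
- The 36% mixes treatment and cancer and is an upper bound on the treated share.
- Table 1 shows current prescriptions in 54.0%. A reader might take these for bone drugs, but the row is undefined and describes the whole cohort of 25,783, not the year-2000 sample.
- Leaving men out of the pilot yield only makes the contact number conservative.
- Treated patients might be wanted. The Background asks for validation in the patients ordinarily seen at each level of care. The limitations section, however, aims the results at people whose risk a physician is evaluating. The article does not settle which reading applies to treated patients, so it has to say.

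**Conclusion.** The inconsistency is established from the text and the arithmetic: the study is sized on one population and its eligibility criteria describe another. The evaluable set differs by 2,385 − 1,377 = 1,008 people between the two readings, or 2,385 − 1,525 = 860 once men are kept in both. These figures assume that the main sample behaves like the pilot.

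A reader might infer a shortfall; there is none, since every reading exceeds 1,177. The defect is in whom the validation describes.

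The effect on calibration is conditional. If the written list governs, treated patients enter the Hosmer-Lemeshow and ROC analyses unrestricted, and observed/expected could fall to about 0.82 to 0.93 at the upper-bound treated share, with less distortion at a smaller share. That rests on an assumed 20% to 50% risk reduction and on treatment not being a FRAX input. It should be resolved before the analysis, because the same data can yield different conclusions about FRAX depending on which passage is followed.

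**What to change.** 1. Make the exclusion list and the pilot exclusions agree.
2. Define the primary validation set by anti-osteoporotic treatment status at the baseline DXA, not by treatment started later, and say so in the criteria. Report baseline-treated patients as a separate stratum, using the drug-use data that the Baseline variables section attributes to the QRF.
3. State one cancer criterion and use it both in the list and in the pilot count.
4. Keep men, as the sampling already does, and recompute the yield. If drug/cancer cases are excluded it is 62/149 = 41.6%, giving 2,829 to contact and 3,395 with 20% added, within the 3,664 already selected. With a narrower cancer criterion the yield would lie between 41.6% and 65.1%.

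Censoring follow-up at the start of later treatment is not proposed. The article shows no treatment start dates, and censoring does not fit the binary Hosmer-Lemeshow and ROC analysis.

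The cost is protocol wording and one stratified report on data the article says were collected at baseline. The downside is a smaller primary set than the written criteria would give, which the sizing already assumes.

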**Figure 1 F1:**
[figure not shown]
**FLOW CHART study**. Participant's selection.

Finally, in the pilot study of 149 patients and after fulfilling the exclusion criteria we obtained a sample of 56 (37.6%) of the 149 cases. With more conservative calculations, a maximum of 3,056 subjects should be contacted plus 20% for safety. Thus 3,664 persons should be contacted, therefore our originally recruited population of 5,813 subjects greater than 40 years of age included in the cohort until the end of 2000 sufficiently guarantees the necessary sample size. Consequently, 3,664 subjects were randomly selected from the 5,813 patients included in the cohort during the year 2000.

A sample will be obtained by months in the year 2000. Ordering will be performed using randomised numbers for each month and the calls will be made in this order until the required number is achieved. The approximate calculation is of 317 cases / month with a range from 190 to 395 cases in the different months of 2000, and the calls will be made until the figure calculated per month is met.

## Overview of outcome measurements

### Data collection

The baseline variables of both BMD and QRF were collected at the time of inclusion (2000). The follow up variables (fractures and incidental falls) will be collected by telephone questionnaire (TQ) during 2010 and the beginning of 2011 to complete the 10 years of follow up. The TQ will collect data regarding the fractures occurring from the time of inclusion until the date of the TQ as well as other information on known factors of fracture risk.

### Baseline variables

These include variables related to the patient: Demographic (date of birth, sex), anthropometric (weight, height, body mass index).

BMD measurement will be determined by central DXA according to the 2004 and 2007 recommendations of the International Society for Clinical Densitometry ISCD (available at: http://www.iscd.org/Visitors/positions/OfficialPositionsText.cfm) for the interpretation of the results using a Lunar GE model "Prodigy Advance" densitometer with 11.4 software and with BMD and T-score determination with NHANES III references. The densitometry diagnostic criteria used are the 1994 WHO criteria which classify the results into 3 groups according to the levels of BMD values of the femoral neck: normal (T-score > -1), osteopenia (T-score between -2.5 and -1) and osteoporosis (T-score ≤ -2.5).

Additional file 1 shows the clinical factors of fracture risk analysed with the structured questionnaire (QRF), dietary intake of calcium and drugs use.

The estimated absolute risk of fracture at 10 years according to the FRAX™ tool is determined through the official web site (available at: http://www.shef.ac.uk/FRAX). The calculations of probability of fracture with or without the T-score will be analysed in parallel by two blinded investigators (patients anonymised and assigned an alphanumeric code). On the appearance of any difference a third and fourth blinded investigator will analyse the results and will recalculate the case.

### Follow up variables

These variables include the appearance of incidental fracture in the last 10 years (dependent variable): the telephone questionnaire will be carried out with a telephone call made after 10 years of follow up. All the fractures will be confirmed through medical records and/or consultations to the health care centres after receiving authorisation from the participants. In all cases the follow up at 10 years will be completed in these subjects. In cases of death, the data related to the cause of death and the appearance of fractures will be requested from the relatives and by record checking.

The number of falls during the last year will be determined with the TQ. Review of the literature has shown different ways to analyse the falls occurring in the study subjects. The most frequently used method is considered in this study which asks about the number of falls during the year prior to the interview and whether a fracture was produced in any of the falls. Other variables to be collected during this period are: the appearance of important diseases, the taking of osteopenic drugs and the use of walking aids. Additional file 2 shows the telephone questionnaire.

### Analysis plan

The characteristics of the population will be described according to univariate descriptive analysis. Simple comparisons of the baseline characteristics will be made among the participants and non participants of the cohort. The Chi-square test will be used to evaluate the association between qualitative variables. The Student's t-test or, if necessary, its non parametric equivalent, the Mann-Whitney U test, will be implemented to evaluate the differences in the distribution of a quantitative variable according to the categories defined by a binary exposure. To assess the differences in the distribution of a quantitative variable according to the categories defined by a categorical variable with more than 2 categories, ANOVA analysis of variance or its corresponding non parametric test (Kruskal-Wallis) will be used.

For the predictive validation of the FRAX™ tool, the appearance of the first fracture occurring during the follow up period will be taken into account. The validation of the results obtained with the FRAX™ will be performed with the Hosmer-Lemeshow test and the calculation of the ROC curve. This test divides the participants into groups (normally 10) based on their estimated risk of fracture (FRAX™) and confirms that each group presents a number of cases of incidental fractures adjusted to the predicted number. On the other hand, the ROC curve considers the scale of FRAX™ risk as a diagnostic test of the presence of future fractures and as such leads to different calculations of sensitivity and specificity changing the cut off point selected. Finally, both probabilities (sensitivity and the complementary of specificity, or 1- specificity) will be graphically represented the curve. The shape of the curve is a visual indicator of the quality of the diagnostic test.

To know the distribution of the factors associated with fracture according to age and sex, bivariate combinations will be used with the Chi-square test among categorical variables and the Student's test among quantitative and categorical variables. To model the number of fractures occurring in our dataset which is, in fact, a count over time, Poisson regression will be used, which is what is precisely required for this type of variables and was used for the creation of the FRAX™ scale. All the statistical tests will be undertaken with a confidence interval of 95% and with the use of the 17th or latest version available of the SPSS statistical package.

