### The FRAX ™ tool, a useful tool for clinical practice

In 2008, the WHO published a new promising tool for the evaluation of absolute risk of fragility fracture: the FRAX™ tool [11], WHO fracture risk assessment tool. This is a scale including 11 of the clinical risk factors which have demonstrated a strong association with the incidence of fracture in previous studies according to the WHO experts. Factor number 12 in this scale also includes a single value of Dual-energy X-ray absorptiometry (DXA) central bone densitometry: the T-score of the femoral neck. An introducing these data of a patient provided in the form of the FRAX™ website, an individualised calculation of the percentage of prediction of absolute risk of: (a) major osteoporotic fracture (clinical vertebral, hip, forearm or humeral fracture) and (b) hip fracture in the following 10 years may be made [11].

To develop the logarithmic formula of FRAX™, were included parameters from different European cohorts from the EVOS study focused on vertebral fractures [12]. As representatives of the Spanish population were included people from Oviedo and other three Spanish cities. However, they had very low rates of response: in some cases were less than 8%, with a total number of subjects potentially insufficient to be representative of Spanish population [13].

On the other hand, it should be pointed out that as recommended in the description of the FRAX™ tool, this scale should be developed and validated in each country. Cost-effectiveness studies are also recommended with the data from each country to obtain an approximation of the cost which each country is willing to accept as reasonable for the prevention of fragility fractures.

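### FRAX is validated against one unspecified first-fracture event, although it predicts two separate 10-year risks

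*Protocol article*

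**What the plan says.** All references are to the protocol article.

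- **What FRAX predicts.** The section on FRAX as a tool for clinical practice lists two outputs: "a) major osteoporotic fracture (clinical vertebral, hip, forearm or humeral fracture) and (b) hip fracture in the following 10 years".
- **What is counted.** Under Analysis plan, "the appearance of the first fracture occurring during the follow up period will be taken into account". Observed and predicted numbers are then compared in risk groups (Hosmer-Lemeshow), and a ROC curve is drawn. No site is named, and nothing says which FRAX output is meant.
- **Other outcome wording.** The Abstract, the Main objective and the enrolment section speak of fragility fractures. Falls and fragility fractures defines these by low-impact mechanism. The limitations section notes that symptomatic vertebral fractures are the ones FRAX covers.
- **When fractures count.** Data collection: "The TQ will collect data regarding the fractures occurring from the time of inclusion until the date of the TQ". The same section says the follow-up variables "will be collected by telephone questionnaire (TQ) during 2010 and the beginning of 2011 to complete the 10 years of follow up". Follow up variables instead has "the appearance of incidental fracture in the last 10 years (dependent variable"), with the call made after 10 years. The Abstract and the enrolment section point to 10 years from the first DXA and questionnaire. On recruitment, Study population says "this sub-cohort included 5,813 persons recruited from January 1 to December 31, 2000".

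**The concern.** A calibration check has meaning only if the observed event is the one whose probability was predicted. Here the prediction is site-specific and comes in two forms, while the event is a single first fracture with no site list. A gap between observed and predicted numbers could then come from the definitions and not from FRAX.

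This touches the main objective. The Discussion says the study should support adjusting FRAX's calibration, so an artefact of definition could be carried into that adjustment. The Discussion also cites studies in which FRAX predicted fewer fractures than were observed. Counting extra sites against FRAX-major pushes the same way and could be mistaken for confirmation.

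**Working it through.** **1. The plan's own figure.** The sample size is 1,070 for 3% precision, two-sided, 95% confidence. No incidence is stated, so I assume the worst case p = 0.5: n = 1.96² × 0.5 × 0.5 / 0.03² = 1,067.1, rounded up to 1,068, which agrees with 1,070. Adding 10 years at 1% a year, 1,070 × 1.10 = 1,177, as stated. On this reading the figure does not depend on how the fracture outcome is defined.

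**2. One event against two outputs.**

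| Reading of the rule | Against FRAX-major | Against FRAX-hip |
|---|---|---|
| Every first fracture counts, whatever the site | Fractures at other sites added; observed too high | Event far too broad; observed much too high |
| First fractures split by site | Other sites drop out; major fractures that follow an earlier fracture elsewhere are missed; observed slightly low | Hip fractures that follow an earlier fracture are missed; observed too low |

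Reading the event as fragility fracture removes high-impact fractures but not low-impact ones at, say, rib, pelvis or ankle. No reading gives both outputs their proper counterpart.

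**3. Size against FRAX-major, first row of the table.** Let s be the share of people counted as events who have a FRAX-site fracture at any time in the 10 years. Someone with a rib fracture and later a hip fracture is a true major case and belongs in s. If FRAX is exactly right, expected = s × observed, so observed/expected = 1/s. The article does not give s; these values are assumptions:

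- s = 1.0: 1.00
- s = 0.9: 1/0.9 = 1.11
- s = 0.8: 1/0.8 = 1.25

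**4. Effect on the Hosmer-Lemeshow test.** Simulation with n = 1,070, 10 groups, 10 degrees of freedom, 5% level, FRAX exactly right for major fracture, and 2,000 runs per cell. Predicted risks follow a gamma distribution with mean 5%, 8% or 12% (assumed), and the excess is proportional across risk levels.

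| Observed/expected | Mean 5% | Mean 8% | Mean 12% |
|---|---|---|---|
| 1.00 | 5.6% | 5.6% | 4.8% |
| 1.10 | 12.4% | 15.1% | 14.5% |
| 1.25 | 30.8% | 42.5% | 61.0% |

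Entries are the percentage of runs in which a correct FRAX is rejected.

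**5. Time window.** Recruitment ran from 1 January to 31 December 2000. I take the last call as 31 March 2011 (assumed; the article says only the beginning of 2011).

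- First person recruited: called at the end of 2010, 11.0 years; called at the end of March 2011, 11.24 years. That is 10% to 12% more than 10 years.
- Last person recruited: called at the end of 2010, 10.0 years; called at the end of March 2011, 10.25 years.

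Counting back 10 years from a call at year 11 drops the first year and adds the eleventh. If each call falls on the ten-year anniversary, the wordings agree.

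**The case against.** The Analysis plan never says that a fracture at any site counts. The article describes both FRAX outputs with their sites, and its remark on symptomatic vertebral fractures shows that the authors wanted to match FRAX's definition. A site list might sit in the full plan, and the telephone questionnaire is in an additional file that is not shown.

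Some of this stands. The rule is better described as unrestricted by site than as a declared all-site outcome. But the article does fix an event for the validation, only the vertebral component is aligned with FRAX, and no hip outcome is defined. The rule as written is unsuitable, which is more than detail left out.

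A reader might also infer that the rule makes FRAX seem to under-predict major fracture and over-predict hip fracture at once. The text does not support that. The first effect needs all first fractures pooled, the second needs them split by site, and no single reading gives both.

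On the window, most of the wording points to 10 years, and sampling by month of recruitment suggests that calls follow enrolment order. It would be wrong to infer that the whole cohort is observed about 12% too long. That figure is an extreme for one person under an assumed closing date.

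**Conclusion.** The concern holds in this form: the stated validation event matches neither FRAX output, so the observed-to-predicted comparison and the ROC curve cannot be interpreted cleanly for either.

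The definitional point needs no assumption. The size does. The 1.11 to 1.25 for major fracture rests on an assumed 80-90% share and on pooling all first fractures. At about those ratios (simulated at 1.10 and 1.25), the planned test would reject a correct FRAX in roughly 12-15% and 31-61% of studies, under assumed mean risks of 5-12%. For hip fracture even the direction depends on the reading, so no figure is given.

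The window is an inconsistency between sections and the smaller part of the problem.

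**What to change.** For the FRAX validation only, replace the first-fracture rule with two outcomes per person:

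1. First major osteoporotic fracture (clinical vertebral, hip, forearm or humerus), compared with FRAX-major.
2. First hip fracture, regardless of any earlier fracture elsewhere, compared with FRAX-hip.

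Count each only if its record-verified date is within 120 months of the baseline DXA and questionnaire, and use the same window wording in Data collection and Follow up variables. Other and later fractures should stay available for the secondary association analyses and the Poisson model of fracture counts.

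**Cost.** Wording only. Confirmation of every fracture through medical records or the health care centres is already planned and should supply site and date; the sample size figure is unaffected. The validation will have fewer events. Under the assumed shares, 10-20% of people counted as events leave the major outcome, and more if other sites are common. The hip outcome, a subset of the major one, can have no more events than it and may be sparse across ten risk groups.
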